### Data management

A project coordinator will help enroll participants and oversee the progress of the study, ensuring that participants’ rights and well-being are maintained. This individual will also ensure adherence to the study protocol, ethical standards, and regulatory requirements. Additionally, the coordinator will be responsible for reporting the proper operation of the eHealth system and the accurate recording of data and will monitor coding, security, and encrypted storage of all collected data.

### Planned data analysis

Data will be entered and analyzed using SPSS version 30. Demographic data will be summarized, with frequency and percentage for categorical variables, and mean and SD for continuous variables. Group difference at baseline will be compared using chi-squared tests for categorical variables and ANOVA for continuous variables. The Pearson correlation will be used to explore the relationship between weight loss and adherence scores. Changes in variables between baseline and the three-month follow-up will be compared using paired t-tests or Wilcoxon signed-rank tests as appropriate. To compare the mean changes in the continuous outcome variables including body weight, waist circumference, BMI, HRV and HRR, sleep quality, nutritional status, self-care capacity, perceived depressive symptoms and stress level, chronic pain among the two groups with the intention-to-treat principle. This approach ensures that all participants are included in the analysis as originally assigned, regardless of their level of compliance, thereby mitigating the impact of missing data. For missing values, methods like multiple imputation and sensitivity analyses will test the robustness of results. Adherence rates will also be analyzed alongside outcomes, using generalized estimating equations to account for repeated measures and reliably estimate intervention effects. Medication use for metabolic diseases and psychosomatic symptoms will be documented at baseline and follow-up, serving as a covariate in analyses to distinguish intervention effects. Subgroup analyses may compare outcomes between medicated and non-medicated participants. As age may significantly influence participants’ responsiveness to the intervention, conducting subgroup analyses by age cohort offers more specific insights into how the intervention may benefit older adults at different stages of aging. Post hoc pairwise comparisons of the changes in the outcome variables across the two study groups will be performed to compare the effectiveness of the EG and the WLCG. All the tests are two-sided and a *p* < 0.05 will be considered statistically significant.

Process evaluation and focus group data will be analyzed using qualitative content analysis. The process evaluation for individual participants and focus groups for intervention providers will be audio-recorded, with relevant portions transcribed verbatim into Chinese and subsequently cross-checked by research assistants and study investigators. Cantonese transcription will be facilitated by AI translation system. The qualitative analysis will employ an inductive thematic analysis approach [83].

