### Intervention materials and theoretical framework

The eHealth system is designed to facilitate the implementation of a personalized, goal-based health care plan, enabling participants to monitor their health vitals at home on a weekly basis and engage in weekly tele-counseling sessions. The system comprises the following components: (1) temperature and oxygen monitoring (single-sided bio-sensing earbud for the right ear); (2) tablet; (3) FDA-certified Bluetooth blood pressure monitor; (4) docking station; (5) USB charging cable; (6) anti-static bag; (7) three ear gels (medium size); and (8) user manual. Additionally, a 5G data plan will be provided to all EG participants. The eHealth system captures seven key health vitals: heart rate, respiratory rate, core body temperature, oxygen saturation (SpO2), HRV as an indicator of mental health, HRR for cardiac health, and blood pressure.

The front page of the eHealth system (Fig. 3) features a visually engaging user interface and user experience design that directs participants to six icons for self-monitoring logbooks and an educational section: (1) daily recording of WFPB dietary details; (2) documenting daily PA, accompanied by relevant video materials; (3) recording mindfulness practices; (4) monitoring and capturing seven health vitals; (5) documentation of a stress diary, thought records, and pleasant events; and (6) comprehensive information on MetS, psychosomatic symptoms and their health risk factors, as well as self-care strategies. Additionally, the eHealth system incorporates a calendar reminder feature for tele-counseling sessions and employs “cues to action,” highlighted in red with an exclamation mark, to promote self-initiated action and self-regulation among participants.

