### Adherence and fidelity

Throughout the 12-week intervention, self-monitoring logbooks within the eHealth system will be utilized to record WFPB diets, PA, and mindfulness practices (Appendix B). Dietary adherence will be quantified using a dietary adherence score derived from the food records. Initially, the food records will be analyzed using Food Processor software, version 11.1, developed by ESHA Research (Salem, Oregon, USA), to determine the nutrient and energy intake associated with each diet plan. Apart from the nutrient and energy intake, it is crucial to assess whether EG participants are consuming a diverse and abundant array of high quality whole plant-based foods, including leafy greens, cruciferous vegetables, rhizomes, solanaceous vegetables, legumes, beans, soy products, whole grains, nuts, and seeds.

Additionally, all EG participants are instructed to wear a single-sided earbud via the eHealth system while watching and following the exercise videos to facilitate simultaneous monitoring and capturing of their health vitals. Regarding mindfulness practices, participants will be required to log whether they engage in meditation, including the duration and types of meditation techniques practiced. Adherence to self-monitoring will be tracked over the course of the 12-week intervention. This adherence will be quantified by calculating the percentage of completed logbooks relative to the total number of logbooks targeted.

Starting in the third week of the intervention, EG participants are required to complete a stress management logbook within the eHealth system (Appendix B). Case managers (CMs), who are registered social workers, will facilitate discussions with EG participants to reinforce and remind them to apply the coping strategies they have learned.

The speech-to-text (STT) software is integrated into the tablet and facilitated by the eHealth system, allowing EG participants to input the aforementioned details either by audio or using a stylus pen for text entry. Audio recordings will be converted to text and transferred to the backend system, where CMs can retrieve and download these text files. CMs are required to review the logbooks and bio-signal files to implement and assess a goal-based health care plan in collaboration with EG participants prior to the weekly tele-counseling sessions. If participants experience any discomfort or difficulties during the intervention period, they will be referred to appropriate specialists.

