### Intervention protocol

The intervention protocol is reported based on Template for Intervention Description and Replication (TIDieR) checklist and guide [79]. Prior to the commencement of the 12-week intervention, a two-day workshop will be conducted to introduce five key domains: (1) health risk appraisal and self-care; (2) PA and self-administrated acupressure; (3) emotion and stress management; (4) WFPB diet, nutrition, and disease relationships; and (5) meditation and mindfulness practices. This workshop is led by a multidisciplinary team comprising the principal investigator, registered TCM practitioner, senior physiotherapist (SPT), fitness trainer, registered dietitian, mindfulness instructor, senior registered nurse, and WFPB medical doctor. CMs are required to attend the workshop to familiarize themselves with the intervention content and the operations of the eHealth system. On the final half-day of the workshop, the eHealth system will be distributed to all EG participants. A briefing and hands-on training session will be organized by the information technology provider and technicians to demonstrate the operation of the eHealth system. All EG participants will be guided to learn self-monitoring logbooks to record their WFPB diet, physical exercise, mindfulness practices and a stress management logbook during the joint training and demonstration. An e2HLE booklet will be provided to all EG participants, encompassing a range of topics (Table 2).

**Table 2 Tab2:** The details of the e2HLE booklet

**Component**	**Details**
PA and self-administrated acupressure	-The importance and key points of PA; warm-up exercise, stretching, balance training, muscle strength training, aerobic exercise, cool down exercise with photos, URL links and QR codes. -The origin, efficacy and operating techniques of acupressure and self-administrated acupressure methods for the twelve most common acupressure points (e.g., GV20 Baihui, GB20 Fengchi, GB21 Jianjing, BL52 Zhishi, LI10 Shousanli, ST36 Zusanli, LI4 Hegu, SP6 Sanyinjiao, BL40 Weizhong, KI1 Yongquan, etc.)

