During the process evaluation sharing sessions, EG participants will be organized into small groups of approximately 10 to 12 individuals (Table 3). Weekly individualized tele-counseling sessions by CMs, each lasting approximately 30 min, will be conducted. These sessions aim to increase motivation, review personalized care plans, and provide general support in making goal-based lifestyle changes and addressing challenges. Mutual support networking will be facilitated regularly between CMs and participants through WhatsApp or telephone communication. Each EG participant will receive a supermarket gift card valued at HKD200 (approximately USD25) as reimbursement for their time and registration fees, as well as an incentive for completing the 12-week intervention and participating in data collection.

WLCG: Participants will receive usual care from the elderly centers for the first three months. For ethical reasons, those in WLCG will crossover to the intervention arm after 12 weeks, receiving the same intervention content, dosage, and duration as the EG participants.

After completing stage one, all participants will attend a swearing-in ceremony where selected individuals will become “Smart Healthy Aging” ambassadors, coaching participants in stage two. This approach follows the Train-the-Trainer (TTT) model [80] and incorporates health coaching [69]. Key trained participants will share their insights, provide ongoing support to new participants, and facilitate the intervention process to build confidence and competence. They will receive a certificate of appreciation during the ceremony. The entire implementation process will be videotaped to create non-commercial documentary clips that aim to synthesize and disseminate evidence on the effectiveness of community-based behavior change interventions to a wider audience.

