### Secondary outcomes

The score range, direction and psychometric details of the secondary outcomes are presented in Appendix C. The secondary outcomes include enhancements in IC, specifically targeting four domains: motor function, vitality (nutrition), psychological well-being, and mental and cardiac health facilitated by the eHealth system. Additionally, improvements are anticipated in at least two of the cardio-metabolic risk factor profiles, including waist circumference, blood pressure, BMI, visceral fat, HbA1c, LDL cholesterol levels, and homocysteine (assessed through blood tests). Other expected outcomes encompass improved sleep quality and reduced chronic pain, decreased depressive symptoms and stress levels, and enhanced self-care capacity and social support.

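### As the article describes it, HRV and HRR have no control-arm reading and no pre-randomisation baseline, yet both are listed as between-group change outcomes

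*Protocol article*

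**What the plan says.** The Planned data analysis section of the protocol article announces an intention-to-treat comparison of the two groups: "To compare the mean changes in the continuous outcome variables including body weight, waist circumference, BMI, HRV and HRR", followed by sleep, nutrition and other scales.

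Where the two variables come from is stated under Intervention materials and theoretical framework. The eHealth system records seven vital signs, among them "HRV as an indicator of mental health, HRR for cardiac health, and blood pressure". The Secondary outcomes section names the matching intrinsic-capacity domain with the words "mental and cardiac health facilitated by the eHealth system".

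Who has the system, and when, is in the Intervention protocol section: "On the final half-day of the workshop, the eHealth system will be distributed to all EG participants". For WLCG the same section says: "Participants will receive usual care from the elderly centers for the first three months", and then that "those in WLCG will crossover to the intervention arm after 12 weeks".

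The Procedure of data collection section puts the baseline questionnaire and health examination (T1) before randomisation and the follow-up (T2) about three months later. It refers to Appendix C for assessment methods. The Randomization section has the allocation envelope opened once the baseline questionnaire is complete.

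**The concern.** A comparison of mean change between arms needs, in each arm, a value at T1 and a value at T2 obtained in the same way. The described source of HRV and HRR is a device that, during the comparison period, only one arm holds and that this arm receives only after allocation. On that description the control arm supplies nothing, and the EG baseline can already be affected by knowledge of allocation and by the workshop.

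Mental and cardiac health is one of the four intrinsic-capacity domains in the hypotheses. The depression and stress questionnaires can inform the mental side in both arms. For the cardiac side, HRR is the only measure the article names. The same section also plans paired pre-post tests, so a within-EG change could still be calculated. It would carry regression to the mean and growing familiarity with the device along with any true effect, and it would have no control arm against which to separate them.

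**Working it through.** The article gives no figure specific to HRV or HRR. The check is therefore a trace of the measurement route, followed by a count.

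**Route**

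| Question | What the article states | Section |
|---|---|---|
| What is compared? | Mean change in HRV and HRR, EG against WLCG | Planned data analysis |
| What measures them? | The eHealth system; no other source is named | Intervention materials; Secondary outcomes |
| When is T1? | Before randomisation | Procedure of data collection |
| When is allocation disclosed? | After the baseline questionnaire | Randomization |
| When does EG get the system? | Last half-day of the pre-intervention workshop | Intervention protocol |
| When does WLCG get the intervention? | After 12 weeks | Intervention protocol |

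A device handed out to EG as a group can only be handed out once group membership is known. The order for EG is therefore T1, allocation, workshop, device. For WLCG it is T1, allocation, usual care, T2, crossover. A first WLCG reading at crossover could at best stand in for T2. It would not give a change score, because there is no T1 reading to subtract.

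**Count by the described route**

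- WLCG with HRV or HRR at T1 or T2: 0 of 75.
- EG with HRV or HRR before randomisation: 0 of 75.

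**Consequence for the estimate**

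The variance of a between-arm difference in mean change is SD² × (1/n_EG + 1/n_WLCG). With n_WLCG = 0 it is undefined, so neither an estimate nor a power can be stated.

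**What the design would otherwise offer**

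- The plan's sample size reproduces. For d = 0.5, two-sided alpha 0.05 and 80% power, n per arm = 2 × (1.96 + 0.84)² / 0.5² ≈ 62.8, so 63 per arm and 126 in total. Then 126 / (1 − 0.1) = 140, as stated.
- With 75 recruited per arm and 8% attrition, 75 × 0.92 = 69 per arm remain.
- Power at d = 0.5 with 69 per arm is Φ(0.5 × √(69/2) − 1.96) = Φ(0.98) ≈ 0.84 (normal approximation).

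Measuring both arms would thus give these two outcomes the same power as the other continuous outcomes, for an effect of that size.

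**Can the missing-data plan repair it?**

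No. Intention to treat fixes who is analysed and in which arm; it creates no observations. Multiple imputation needs observed values from which to model the missing ones. With none in WLCG, the imputed control values, and so the estimated effect, would come from the modelling assumption alone.

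**The case against.** The strongest reply is that handing out home kits is not the same as measuring an outcome. The article sends the reader to Appendix C for assessment methods, and that appendix is not shown. The T1 and T2 health examinations are not restricted to EG, and blinded assessors at follow-up presuppose that both arms are seen. A centre-held unit could supply HRV and HRR on that schedule. The Secondary outcomes wording about the eHealth system can also be read as the system helping the improvement, not measuring it.

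Part of this stands. A reader might infer that the trial definitely has no control data for HRV and HRR. The documents do not say so; they only fail to describe any way of obtaining such data. The reply does not remove the conflict, however. The article says that the system captures these two variables, names no alternative, and describes its distribution to EG only after allocation.

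Two further inferences are tempting and should not be drawn:

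- **Exercise state.** The Adherence and fidelity section says that "all EG participants are instructed to wear a single-sided earbud via the eHealth system while watching and following the exercise videos". A reader might conclude that the outcome values mix rest and exertion. Nothing says that these recordings supply the T1 or T2 values, and weekly monitoring of vital signs is described separately.
- **Blood tests.** The abstract mentions pretest and posttest assessments, blood tests included, for EG. A reader might conclude that WLCG has no blood results. The section on blood tests restricts only the result-explanation sessions to EG, not the blood draw. The abstract sentence also covers surveys and health examinations, which the data-collection section does not limit to EG.

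**Conclusion.** The point holds as a conflict between a stated analysis and the stated measurement route. As described, no WLCG participant has an HRV or HRR value at T1 or T2 and no EG participant has one before randomisation, so the between-group comparison of these two outcomes cannot be run. An EG-only change would be a before-after observation, not a randomised effect.

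This rests on one assumption: that Appendix C does not already place an HRV and HRR reading in both arms at both times. If it does, one clarifying sentence in the article settles the matter.

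The reach is limited. Two secondary variables are affected, and with them the cardiac part of one intrinsic-capacity domain. The primary outcome is untouched. Blood pressure is also captured by the system but could be taken at the health examination, so the point does not extend to it. It is worth settling early, because a pre-randomisation value cannot be recovered once a participant has been allocated.

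**What to change.** Choose one of two changes and state it in the article's outcome and analysis sections.

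1. **Measure in both arms.** Record HRV and HRR in every participant at the T1 health examination, before the envelope is opened, and again at T2. Use the same device and one written procedure: a resting recording for HRV and one identical recovery procedure for HRR. State that these readings, not the home recordings, are the outcome values. The cost is a few minutes per visit, on devices the trial already deploys.
2. **Withdraw the comparison.** Remove HRV and HRR from the between-group list in Planned data analysis. Report them descriptively as EG monitoring data, with no claim of effectiveness. The cost is a text edit.

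If Appendix C already provides for the first option, add a sentence saying so. For participants already allocated without a T1 reading, only the second option remains.

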### Pre- and post- blood tests

A total of 20 ml of blood will be drawn and tested by medical professionals in a designated laboratory. The blood tests will cover five main categories: (1) Albumin (nutritional marker); (2) CRP (inflammation marker); (3) Total blood cell count, creatinine, BUN, liver function tests, blood sugar levels, and HbA1c (indicators of anemia, diabetes, and organ function); (4) Total cholesterol, HDL, and LDL levels (cardiovascular disease risk factors); and (5) Homocysteine (indicating potential vitamin B-12 or folate deficiency). Individualized sessions lasting 15 to 20 min will be held for all EG participants after receiving their pretest and posttest blood reports, approximately 2 to 3 weeks after the intervention starts and ends. During these sessions, a registered dietitian and/or a WFPB medical doctor will provide explanations and advice for follow-up care. If any blood test results are abnormal, appropriate referrals for further treatment will be recommended.

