A key strength of this study is the implementation of an eHealth system that allows participants to monitor their bio-signals at home, promoting self-care and self-management in line with goal-based self-regulation theory. This system enhances adherence through self-monitoring logbooks and features simplified functionality via STT software, making it accessible even for illiterate participants. Many older adults expressed a need for such technology during the pilot study in 2021/22, as concerns about usability and device compatibility often hinder their engagement with mobile phones. The digitization of the multi-component lifestyle intervention improves accessibility and flexibility, potentially increasing motivation for behavioral change.

The study also introduces a WFPB diet, trialed for the first time in a Chinese context, encouraging participants to consume a diverse range of high-quality plant foods. Given that changes in dietary habits require comprehensive, systematic guidance with well-defined objectives, participants will be supported by a registered dietitian in establishing realistic, personalised dietary goals, with adherence monitored through the submission of food diaries within the eHealth system. Furthermore, all EG participants will receive individual counselling following both pretest and posttest blood reports, enabling ongoing assessment of their progress, identification of challenges, and reinforcement of their commitment to healthy eating practices. This research aims to clarify the effects of a WFPB diet on metabolic health, emotional stability, psychological well-being, and pain relief, enhancing understanding of the relationship between MetS and psychosomatic effects.

Additionally, the intervention includes a buddy-assisted approach and TTT initiative, fostering social support and health coaching. This collaborative model promotes a communal health culture, normalizing positive behaviors and enhancing program sustainability as trained participants can effectively deliver the intervention to others.

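### Medication recorded at follow-up is made a covariate, although the intervention itself can change it, so the adjusted estimate is not the effect of the package

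*Protocol article*

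**What the plan says.** All places are in the protocol article.

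- **Planned data analysis, the covariate.** Medication use is "documented at baseline and follow-up, serving as a covariate in analyses to distinguish intervention effects". The sentence names both time points, does not restrict the covariate to the baseline value, and names no outcome, so on its face it reaches body weight, the primary outcome.
- **Planned data analysis, the comparison.** Mean changes are to be compared "among the two groups with the intention-to-treat principle".
- **Planned data analysis, the subgroup.** "Subgroup analyses may compare outcomes between medicated and non-medicated participants". No time point is given for being medicated.
- **Procedure of data collection.** Baseline (T1) is completed before randomization and T2 is about three months later.
- **Pre- and post- blood tests.** "Individualized sessions lasting 15 to 20 min will be held for all EG participants after receiving their pretest and posttest blood reports". The first session falls two to three weeks after the start. It is held by a dietitian and/or a doctor and includes advice on follow-up care. The Discussion repeats that "all EG participants will receive individual counselling following both pretest and posttest blood reports".
- **Intervention protocol.** At the workshop "the eHealth system will be distributed to all EG participants". EG participants continue treatment already prescribed. The waitlist control group (WLCG) has usual care for the first three months.
- **Adherence and fidelity.** Before the weekly tele-counseling, "CMs are required to review the logbooks and bio-signal files". The same section adds: "If participants experience any discomfort or difficulties during the intervention period, they will be referred to appropriate specialists".

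**The concern.** A covariate in a randomized comparison should be fixed before randomization, or at least be something that assignment cannot affect. Follow-up medication is neither. EG participants have their blood results discussed with a clinician and their home vital signs looked at every week, and either can lead to a drug being started or changed before T2. The programme also aims to improve blood pressure, HbA1c, LDL cholesterol, depressive symptoms and pain, which are the kinds of condition these drugs treat, so use could equally fall in EG.

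Conditioning on such a variable does two things. It removes whatever part of the effect runs through medication. If an unmeasured factor such as disease severity drives both medication and outcome, it also adds bias that randomization had excluded. The estimate that results no longer answers the question in the Discussion, which is the whole package against usual care.

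The direction depends on facts not known in advance. If EG adds drugs that improve the outcome, the adjusted effect is too small. If drug use mainly marks sicker participants, it is too large. If use falls in EG, both signs reverse. The unadjusted randomized comparison has none of these problems.

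**Working it through.** **1. The plan's own figure.** Sample size section: effect 0.5 SD, 80% power, two-sided 5%.

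- n per arm = 2 × (1.96 + 0.8416)² / 0.5² = 62.8, so 63 per arm and 126 in total.
- 126 / (1 − 0.1) = 140. The stated 140 reproduces.
- Recruited: 75 per arm. With the pilot attrition of 8%, 75 × (1 − 0.08) = 69 per arm are analysed. This is used below.

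**2. Size of the shift.** In a linear model with arm and follow-up medication:

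unadjusted effect − adjusted effect = (EG − WLCG difference in follow-up medication) × (within-arm slope of outcome on medication).

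Neither factor is in the article. Assumed ranges: a difference of 2 to 20 percentage points and a slope of 0.25 to 1.0 SD.

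- Smallest: 0.02 × 0.25 = 0.005 SD, and 0.005 / 0.5 = 1% of the planned effect.
- Largest: 0.20 × 1.0 = 0.20 SD, and 0.20 / 0.5 = 40%.

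**3. Consequence for the test.** Two-sided 5% z-test with noncentrality d × √(69/2) = 5.874 d. With d = 0.5 and no shift, 5.874 × 0.5 = 2.937, and power is Φ(2.937 − 1.96) = 83.6%. With shift s, a true zero effect is tested at d = s. A true 0.5 SD with the shift towards zero is tested at d = 0.5 − s.

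| Medication difference | Shift (slope 0.25 to 1.0) | Significant when the package effect is zero | Power at 0.5 SD, shift towards zero |
|---|---|---|---|
| 2 points | 0.005 to 0.02 SD | 5.0% to 5.2% | 82.8% to 80.5% |
| 5 points | 0.0125 to 0.05 SD | 5.1% to 6.0% | 81.7% to 75.3% |
| 10 points | 0.025 to 0.10 SD | 5.2% to 9.0% | 79.7% to 65.2% |
| 20 points | 0.05 to 0.20 SD | 6.0% to 21.7% | 75.3% to 42.2% |

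**4. Simulation at trial size.** 4,000 runs per cell, 69 per arm, 40% medicated in WLCG (assumed), slope 1.0 SD, true package effect zero.

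- Drug improves the outcome, 10-point difference: unadjusted mean 0.00 SD, 5.1% significant. Adjusted mean 0.10 SD against EG, 9.5% significant.
- Drug improves the outcome, 20 points: unadjusted 0.00 SD, 5.1%. Adjusted 0.20 SD against EG, 21.3%.
- Drug use only marks sicker participants, 20 points: unadjusted 0.00 SD, 4.8%. Adjusted 0.20 SD in favour of EG, 26.7%. This exceeds the 21.7% in the table because the residual SD is smaller in this scenario.
- True effect 0.5 SD, 20 points: adjusted 0.30 SD if the drug helps, 0.70 SD if it marks sicker participants.

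**5. Independent large-sample check.** 400,000 simulated participants, true total effect −0.50 SD, drug effect from −0.5 to +0.5 SD, with and without an unmeasured common cause of medication change and outcome. The unadjusted comparison returned about −0.50 SD throughout. The adjusted one gave:

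| Medication change, EG vs WLCG (assumed) | Adjusted estimate |
|---|---|
| 10% vs 10% | −0.50 SD |
| 15% vs 5% | −0.40 to −0.55 SD |
| 20% vs 5% | −0.36 to −0.57 SD |
| 30% vs 5% | −0.27 to −0.63 SD |

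The bias therefore needs a difference between arms. With equal rates there is none.

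**The case against.** The strongest reply is that the sentence may mean less than it says. It fixes no model, coding or time point. Validity and reliability says that baseline differences will be accounted for, which fits a baseline covariate with the follow-up record kept for description, and a condensed article may leave coding to the full plan. That reading is possible. It is not what the sentence states: it names both time points and gives separation of intervention effects as the purpose, which is what follow-up medication would be used for. If baseline was meant, the correction only clarifies.

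The second reply is that the mechanism is inferred. No passage says that a component starts or stops a drug, EG participants continue prescribed treatment, the case managers are social workers, and the blood-report session is short and may be held by a dietitian alone. This limits how large a difference one should expect, and it stands to that extent. But continuing existing treatment does not exclude new or changed treatment, and recording medication again at follow-up anticipates change. The point needs neither blood drawn in WLCG nor any reading of whom the referral sentences cover.

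Third, intention-to-treat concerns who is analysed and in which arm, and covariate adjustment moves nobody. A lifestyle effect apart from drugs may also be a deliberate second question. Both are fair. The harm arises if that estimate stands in for the effect of assignment, and the text does not keep the two apart.

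Finally, the magnitude rests on assumed inputs, and no reason is given to expect a slope of 1.0 SD on body weight. That stands. The subgroup point is likewise conditional: it applies only if medicated status is taken at T2.

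**Conclusion.** The concern holds, and it should be fixed. As written, the plan conditions on a variable measured after randomization that assignment can change, so the adjusted estimate is not the effect of the package against usual care. This is a fault in kind; the article gives no medication rates from which to derive its size. Under the assumed ranges it runs from negligible (a 2-point difference) to serious (20 points with a slope of 1.0 SD: power of 42.2% in place of 83.6%, or a false-positive rate of 21.7%). The sign is unknown beforehand, so it cannot be allowed for when the results are read. Confidence is medium, because a baseline-only intention cannot be ruled out and because a between-arm difference in medication is plausible but not documented. Baseline medication is a sound covariate, and the unadjusted randomized comparison is unaffected.

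**What to change.** Replace the covariate sentence and the medication-subgroup sentence in Planned data analysis with:

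> Medication use at baseline (T1) will be a covariate in the between-group analyses, and the medicated and non-medicated subgroups are defined at T1. Medication change from T1 to T2 will be compared between groups as an outcome. Any model that includes follow-up medication is exploratory and does not replace the intention-to-treat estimate.

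The cost is this edit to the text. Medication is already recorded at both times, so no data, visits or participants are added and care in WLCG is unchanged. The medication-separated estimate remains available as an exploratory result. Settling this before analysis also avoids choosing between models after the results are seen.
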